## Methods and designs

2

### Study design and settings

2.1

This research is designed as a multicenter prospective cohort study conducted at 4 medical centers, including Huangshi Hospital of TCM (Huangshi City, Hubei Province), LaoHeKou Hospital of TCM (LaoHekou City, Hubei Province), Hubei Provincial Hospital of TCM (Wuhan City, Hubei Province) and LongHua Hospital Shanghai University of TCM (Shanghai City, Shanghai). LongHua Hospital Shanghai University of TCM is the leading medical center. These 4 TCM hospitals are the main medical institutions responsible for the treatment of COVID-19 patients. In order to strengthen the cooperation, we will establish a coordination center. This center contains medical experts, statisticians and quality control experts from other hospitals and universities. The primary function of this center is to provide vital clinical decisions or recommendations, conduct data statistic, monitor the research process.

### Objectives

2.2

The main aim of our trail is to investigate the efficacy and safety of *Baidu Jieduan Granule* in the common type of COVID-19 patients and assess mental health outcomes through our 1year follow-up.

### Population

2.3

For this multicenter prospective cohort study, we will enroll 300 COVID-19 patients meeting the inclusion criteria from 4 medical centers. The recruitment duration will be lasted from February 2020 to June 2020; the follow-up will end on June 30, 2021. The study flowchart is as Figure 1.

**Figure 1 F1:**
[figure not shown]
Flowchart of study design.

### Inclusion criteria

2.4

1.Patients diagnosed with COVID-19^[20]^1)Meeting one of the following evidences:1.Real-time reverse transcription-polymerase chain (RT-PCR) detection of new coronavirus nucleic acid shows positive.2.The tested virus gene is highly homologous to SARS-CoV-2.3.Serum SARS-CoV-2 lgM and lgG antibody are positive.4.Serum SARS-CoV-2 IgG antibody turns positive or the serum novel coronavirus specific IgG antibody in the recovery phase is 4 times or higher than that in the acute phase.2)Patient has the symptoms of cough, expectoration, chest pain, dyspnea, and fever.3)Imaging findings of pneumonia.2.18 years old ≤ age ≤80 years old;3.Informed consent, participate in this study voluntarily.

### Exclusion criteria

2.5

1.The patient was allergic to *Baidu Jieduan Granule.*2.Pregnant and lactating women.3.Patients with obstructive pneumonia, pulmonary interstitial fibrosis, pulmonary alveolar proteinosis and allergic alveolitis caused by lung tumor4.Patients with a malignant tumor, liver cirrhosis, chronic renal failure (uremic stage), hematological disease, HIV, and other serious diseases.5.Patients who were treated with hormones and immunosuppressant for a long time.6.Patients who suffer from severe mental illness or are unable to cooperate with this experiment.

### Patient withdrawal

2.6

1.Subjects experiencing serious adverse events at any time during the treatment period.2.Subjects giving up the study midway.

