### Sample size

2.7

Considering that COVID-19 is a newly emerging infectious disease, and it is the first time we use *Baidu Jieduan Granule* for the treatment of COVID-19, there are no reference resources at present that we cannot calculate the exact sample size. We suppose that the withdrawal rate is about 10%^[21]^ and about 300 patients that will be enrolled in our study, and an average of 75 patients will be admitted to each medical center. The collected data will provide a basis for calculating sample size in future and facilitate the future research.

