#### Primary outcomes

2.10.1

The primary outcomes of our study are clinical outcomes. In our study, there are 4 kinds of clinical outcomes:

1.recovery, the following conditions shall be met:1.the body temperature is normal for 3 consecutive days2.respiratory symptoms disappeared completely,3.the nucleic acid test of respiratory tract samples is negative for 2 consecutive times (the sampling interval is at least 1 day);2.condition improved, meet any of the following 2 items:1.the clinical symptoms are significantly relieved,2.the nucleic acid of sputum, nasopharynx test paper and other respiratory tract samples are negative for 2 consecutive times (the sampling interval should be at least 24 hours);3.condition worsen, one of the following situations occurs:1.shortness of breath, respiratory rate (RR) ≥30 times/minutes,2.oxygen saturation ≤93% in resting state,3.arterial oxygen partial pressure (PaO2) / fraction of inspired oxygen (FiO2) ≤300 mm Hg,4.shock,5.respiratory failure, requiring ventilator support,6.organ failure needing intensive care, and7.death.

We count the number of patients of each kind of clinical outcomes then calculate the ratio.

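### Withdrawing patients for any serious adverse event overlaps with the gravest part of the primary 'worsen' category, so the worst outcomes may be lost from the primary ratio

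*Protocol article*

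**What the plan says.** Section 2.6 (Patient withdrawal) of the protocol article has two items: "Subjects experiencing serious adverse events at any time during the treatment period" and "Subjects giving up the study midway".

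Section 2.10.1 states: "The primary outcomes of our study are clinical outcomes". Its 'worsen' category is met by any one of seven criteria. The first three are physiological thresholds (respiratory rate, saturation, PaO2/FiO2), for example "oxygen saturation ≤93% in resting state". The fourth is shock, and the list ends: "5.respiratory failure, requiring ventilator support,6.organ failure needing intensive care, and7.death". The summary is: "We count the number of patients of each kind of clinical outcomes then calculate the ratio". No denominator is given.

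Table 1 marks clinical outcomes at D14 only. Section 2.7 allows for about 10% withdrawal among about 300 patients. Section 2.10.4 words an adverse event as an adverse reaction under normal usage and dosage, decided by a clinical expert of the coordination center. It does not define 'serious'. Section 2.11 plans a year of telephone follow-up for all patients, starting after the two treatment weeks.

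**The concern.** A patient who is ventilated on day 5 has met the primary 'worsen' category and, in the usual meaning of 'serious', also a ground for withdrawal. If that patient leaves the study, it happens before the only scheduled assessment of clinical outcome, and it happens because of that outcome. Loss of this kind is informative. It lowers the observed worsening rate wherever it occurs. If it is more frequent in one group, it shifts the comparison in favour of that group.

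Section 1 gives the purpose of the treatment strategy as keeping common-type patients from becoming severe or critical. The patients at risk of being lost are the ones who bear on that claim.

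**Working it through.** **1. What withdrawal means.** Three places suggest leaving the study rather than stopping the granule:
- The second item of section 2.6 concerns patients who give up the study.
- Section 2.7 treats withdrawal as attrition.
- Section 2.10.3 deals separately with stopping the drug. The control group receives no granule (section 2.9), so for controls the rule cannot mean stopping it.

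**2. How far the rule and the endpoint overlap.** Criteria 4 to 7 would ordinarily be serious adverse events. Criteria 1 to 3 need not be. The overlap is partial.

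**3. Whether later follow-up repairs the loss.** The telephone phase begins after the two weeks, and Table 1 schedules only the LSAs and DASS21 in it. It is not set up to recover D14 clinical outcome.

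**4. The plan's own figures.** 4 centers × 75 = 300. 10% of 300 = 30, leaving 270. These reproduce. The article states no event rate, effect or power, so every rate below is an assumption.

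**5. Formula.** Let p be the true worsening rate and f the share of worsened patients who are withdrawn and not counted. The observed rate is p(1 − f) / (1 − pf).

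**6. No true effect, unequal loss, 150 per group.** For p = 20%:
- f = 50%: 0.10 / 0.90 = 11.1%
- f = 25%: 0.15 / 0.95 = 15.8%
- f = 75%: 0.05 / 0.85 = 5.9%

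The number lost is 150 × p × (sum of the two shares).

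| True rate, both groups | Share lost, granule v control | Observed, granule v control | Spurious difference (points) | Expected number lost |
|---|---|---|---|---|
| 10% | 50% v 25% | 5.3% v 7.7% | 2.4 | 11.25 |
| 10% | 75% v 25% | 2.7% v 7.7% | 5.0 | 15 |
| 20% | 50% v 25% | 11.1% v 15.8% | 4.7 | 22.5 |
| 20% | 75% v 25% | 5.9% v 15.8% | 9.9 | 30 |
| 30% | 50% v 25% | 17.6% v 24.3% | 6.7 | 33.75 |
| 30% | 75% v 25% | 9.7% v 24.3% | 14.6 | 45 |

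Swapping the shares between groups reverses the sign. The two 30% rows need more withdrawals than the plan's 30. Within 30, the largest difference in the table is 9.9 points, and that row uses the whole allowance.

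**7. Equal loss.** If half of the worsened patients are lost in both groups, an assumed 20% v 10% becomes 11.1% v 5.3%. Power falls from 68% to 43% (150 per group enrolled; two-sided 0.05 assumed, because the article does not state sidedness). For 10% v 5% it falls from 38% to 22%, and for 30% v 15% from 88% to 65%.

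**The case against.** A reader might infer that the plan removes the worst outcomes from the comparison. The article does not say so. It never states that withdrawn patients are dropped from the ratio, and analysis sets may be defined in a full protocol or analysis plan that is not shown. Listing death as a primary component would make little sense if deaths were deleted. The 'worsen' category is worded as an event that occurs, so an event on day 5 could be classified when outcomes are tabulated at D14. These points stand, and the conclusion is therefore that outcomes may be lost, not that they are.

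A reader might also equate serious adverse events with the 'worsen' outcome. That goes too far, because criteria 1 to 3 need not be serious events. In addition, under the adverse-reaction wording of section 2.10.4, progression of COVID-19 might not trigger withdrawal at all. This also stands, but it does not remove the problem. On that reading, withdrawal depends on an expert's judgement of drug relatedness, the treatments differ visibly, and no blinding is described. A ventilated granule patient could be judged to have a reaction and be withdrawn, while a similar control stays and counts as 'worsen'. Differential loss then becomes more likely.

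Nor do the documents support the claim that the bias must hide harm. Its direction depends on which group loses more worsened patients.

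It can be said, finally, that this is detail properly left to the analysis plan. That holds for the denominator. It does not hold for the withdrawal rule, which the article itself states and which governs what data are collected. An analysis plan cannot restore a D14 status that was never observed.

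**Conclusion.** The concern holds in conditional form. The withdrawal rule in section 2.6 overlaps with 'worsen' criteria 4 to 7, clinical outcome is recorded only at D14, and the article does not reconcile the two. The worst outcomes may therefore be lost from the primary ratio, with a bias that can go either way and may differ by group.

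On assumed worsening rates of 10% to 30% with no true effect, and with 50% v 25% or 75% v 25% of worsened patients lost, the spurious difference runs from 2.4 to 14.6 points. The rates and the shares lost are illustrations, not estimates from this trial. The illustration also assumes that withdrawn patients are not counted, which the article leaves open.

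**What to change.** Reconcile sections 2.6, 2.10.1 and 2.10.4 as follows:
- Define 'serious adverse event', and say whether disease progression counts as one.
- State that stopping study drug is separate from leaving the study.
- Keep patients with a serious adverse event under observation to D14 unless they withdraw consent.
- Count every enrolled patient in the denominator of the original group, and count as 'worsen' anyone who met a 'worsen' criterion or died by D14, whether or not withdrawn.

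Section 4.1 says that the trial is already in follow-up, so an amended sentence cannot recover observations that were not made. Where treatment periods are complete, apply the last item as the analysis rule, using events already recorded on the CRF, and report by group how many patients were withdrawn for a serious adverse event.

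The cost is a short amendment, an analysis-set definition and a little more data retrieval. Worsening rates may come out higher than they would under exclusion. No view is taken on when treatment should stop.

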### Sample size

2.7

Considering that COVID-19 is a newly emerging infectious disease, and it is the first time we use *Baidu Jieduan Granule* for the treatment of COVID-19, there are no reference resources at present that we cannot calculate the exact sample size. We suppose that the withdrawal rate is about 10%^[21]^ and about 300 patients that will be enrolled in our study, and an average of 75 patients will be admitted to each medical center. The collected data will provide a basis for calculating sample size in future and facilitate the future research.

### Grouping

2.8

Three hundred COVID-19 cases aged 18 to 80 years are assigned into 2 groups (experimental group and control group) basing on whether they use *Baidu Jieduan Granule* at a ratio of 1:1. The experimental group and the control group are paired with gender, age and basic diseases so that they are comparable.

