## Introduction

1

Since December 2019, patients with pneumonia-like symptoms of unknown origin was found 1 after other in Wuhan city, Hubei Province.^[1,2]^ Soon after the outbreak, researchers obtained the whole genome sequence by sequencing from the patients samples, and the result revealed that it was a novel coronavirus (COVID-19).^[1]^ The International Committee on Taxonomy of Viruses (ICTV) named the virus as severe acute respiratory syndrome coronavirus 2 (SARS-CoV-2). This kind of virus spread quickly between humans, leading to a worldwide pandemic. As of May 20, 2020, more than 4.7 million people across 215 countries or territories have been infected, of which more than 316 000 cases died.^[3]^ In February 2020, the WHO (World Health Organization) declared the outbreak as the public health emergency of international concern (PHEIC) for the situation getting worse and worse.^[4]^ Therefore, how to prevent and cure this kind of new infectious disease is of high significance.

Analyzing some retrospective studies of COVID -19 cases,^[5,6]^ the commonest manifestations were respiratory and digestive symptoms. Those severe patients could rapidly progress to acute respiratory distress syndrome, septic shock, refractory metabolic acidosis, and coagulation dysfunction, resulting in life-threatening. Currently, there is no specific medicine for the treatment of COVID-19. As we know, most antiviral drugs undergoing clinical testing in patients with COVID-19 are originally developed against influenza, HIV, Ebola, SARS, and MERS.^[7,8]^ But their effects and safety remain unknown. Furthermore, some findings suggest that psychiatric complications for people affected by COVID-19 are universal including post-traumatic stress symptoms (PTSS)/post-traumatic stress disorder (PTSD), anxiety and depression. Experts point out the need to pay specific attention to them at risk of further distress that may need tailored interventions.^[9]^

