### Data collection and management

2.14

We design the case report form (CRF) table as it presented in Additional file 5 by our study protocol. After collecting the information of patients, we will complete the CRFs rightly and timely. Then we input and organize them into an excel sheet. Finally, we will hand it over to statistical experts who will perform statistical analysis. The units of measurement should be unified. We will keep the personal and medical information of all patients strictly confidential. Statistical analysis results will be presented by publishing articles in professional journals or websites after finishing this study. The study procedure and assessments flowchart are as Table 1.

**Table 1 T1:** Study procedure and assessment.

		Observation node					Follow-up phase				
Study period	Visiting items	D1	D3	D5	D7	D14			1 year		
Screening stage	Inclusion criteria	X									
	Signing informed consent	X									
	Exclusion criteria	X									
	Matching and distribution	X									
Observation stage	Administration of study drug	X	X	X	X	X					
	Demographic	X									
	General Condition	X									
	Primary disease	X									
	Complication	X									
	Vital signs	X	X	X	X	X					
	Oxygenation index	X	X	X	X	X					
	Oxygen saturation	X	X	X	X	X					
	Chest CT	X		X		X					
	Hepatic function	X	X	X	X	X					
	Renal function	X	X	X	X	X					
	Cardiac function	X	X	X	X	X					
	Inflammatory indicators	X	X	X	X	X					
	Coagulation function	X	X	X	X	X					
	APACHEII score	X	X	X	X	X					
	Adverse event recording	X	X	X	X	X					
	Drug delivery/taking back/ destruction	X	X	X	X	X					
	Clinical outcomes					X					
	Safety evaluation	X	X	X	X	X					
Follow-up phase	LSAs								X		
	DASS21								X		

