## Discussion

3

To our knowledge, although a lot of countries around the world are accelerating SARS-CoV-2 vaccine development, but no one is available until now for challenges of technical barriers.^[24]^ Furthermore, some COVID-19 patients could finally develop new problems, such as physical disability, cognitive impairment, psychological distress and symptoms of mental illness, increased vulnerability to recurrent infection further health deterioration.^[25]^ The SARS-CoV-2 might coexist with humans for a long time, just like influenza and chickenpox.^[26]^ A study conducted by Havard University projected that we may be confronted with another round of COVID-19 outbreak in winter.^[27]^ Therefore, it is critically important and urgent to find effective drugs or treatments and or preparation for the possible outbreak in the future. We also should keep an eye on prolonged mental illness of COVID-19 recovery patients.

TCM has long experience in treating pandemic and endemic diseases for almost thousand-of-years. In fact, the Chinese government attaches great importance to the role of TCM in the prevention and treatment of SARS-CoV-2, and for the first time that TCM as an independent therapy included in the guideline to diagnoses and treat COVID-19.^[28]^ Moreover, the total number of patients with diagnosed COVID-19 that treated by TCM is around 60,107.^[29]^ In 102 cases of the common symptoms treated with pure TCM, the clinical symptom disappearance time, the recovery time of body temperature, and the average length of stay in hospital were shortened by 2 days on average compared with control group. Both the rate of CT image improvement and the cure rate were increased by 22% and 33%. Also, TCM prevents 24% of the patients from common type to severe and critical forms.^[30]^

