It is inspiring that lots of clinical trials are conducted and reported to evaluate the efficacy of TCM in treating SARS-CoV. However, most of them are poorly designed and lack of persuasion. In our multicenter prospective cohort study, *Baidu Jieduan Granule* we used is under the guidance of the theory “ Internal and External Relieving -Truncated Torsion ” and take the clinical characteristics of COVID-19 patients into consideration. By observing the changes in various indicators and imaging examination results during the disease, we seek to reveal the effectiveness and possible mechanism of *Baidu Jieduan Granule* in the treatment of COVID-19 using statistical analysis. Meantime, we expect to observe the safety and long-term mental health outcomes through follow-up.

This study has several limitations. First, we do not adopt randomized controlled clinical trials. Second, we only involve the common type of COVID-19 patients. Third, our follow-up time is not long enough.

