### Trial status

4.1

This protocol version is 2.0. This trial started on February 1, 2020, and is in the fellow-up phase at present.

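### The groups are called comparable after pairing on gender, age and basic diseases alone; enrolment month over a five-month recruitment is neither limited within pairs nor adjusted for, so the D14 comparison is open to calendar-time confounding if practice shifted.

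*Protocol article*

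**What the plan says.** Protocol article, section 2.8 (Grouping): patients enter a group "basing on whether they use *Baidu Jieduan Granule* at a ratio of 1:1", and then "The experimental group and the control group are paired with gender, age and basic diseases so that they are comparable". Three pairing factors are named; enrolment date is not among them.

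Section 2.3 (Population): "The recruitment duration will be lasted from February 2020 to June 2020". Section 4.1 (Trial status): "This trial started on February 1, 2020", and the study is now in follow-up.

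Table 1 in section 2.14 places "Matching and distribution" at D1. D1 is each patient's own first study day, so this entry sets no calendar distance between the members of a pair.

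Section 2.12 (Statistical analysis) compares groups by t-test or a nonparametric test, rates by chi-squared, and survival by a logistic test. No term for calendar time appears. The Discussion gives as a limitation: "First, we do not adopt randomized controlled clinical trials".

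**The concern.** Pairing can balance only the factors it uses. Because treatment is not assigned at random, the mix of enrolment months can differ between the groups even when every pair agrees on gender, age and basic diseases. A February control may be paired with a May granule user and satisfy the rule.

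This does harm only if two things hold together: the share of patients receiving the granule changed over the recruitment months, and so did background care or outcomes. If both hold, part of the D14 difference in recovery or worsening reflects when patients were treated. The direction is open. The granule would look better if its users cluster in the better months and worse if they cluster in the poorer ones. A larger sample does not reduce a bias of this kind.

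The comparator leaves room for change, because section 2.9 describes it only as conventional or standard Western medicine without naming a regimen. The statement that the pairing makes the groups comparable is therefore stronger than three patient characteristics can support.

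**Working it through.** **The plan's own figures.** Section 2.7 gives an average of 75 patients at each of 4 centres: 4 × 75 = 300, which reproduces. With about 10% withdrawal, 300 × 0.9 = 270, or 135 per group at 1:1. From 1 February to 30 June 2020 is 151 days, so the rule allows a gap of up to about five months within a pair.

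**Assumptions, not in the documents.** Recruitment is split into an early and a late period. Early D14 recovery is 60% and late recovery is 60% + t. The late share is 0.5 + d/2 among granule users and 0.5 − d/2 among controls. The granule has no effect. The test is two-sided at 0.05; section 2.12 gives the 0.05 level but not the sidedness.

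**Formulas.**
- Expected recovery, controls: p_c = 0.60 + t(0.5 − d/2)
- Expected recovery, granule: p_g = 0.60 + t(0.5 + d/2)
- Bias: p_g − p_c = d × t
- Standard error: SE = √{[p_c(1 − p_c) + p_g(1 − p_g)]/135}
- False-positive rate: Φ(bias/SE − 1.96) + Φ(−bias/SE − 1.96)

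**Results.**

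| Scenario | d | t | p_c | p_g | Bias | SE | Bias/SE | False positives |
|---|---|---|---|---|---|---|---|---|
| Mild | 0.2 | 0.1 | 64% | 66% | 2 points | 0.058 | 0.34 | 0.064 |
| Moderate | 0.3 | 0.2 | 67% | 73% | 6 points | 0.056 | 1.08 | 0.190 |
| Extreme | 0.4 | 0.3 | 69% | 81% | 12 points | 0.052 | 2.30 | 0.633 |

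The extreme row needs recovery to rise from 60% to 90% and a late share of 70% in one group against 30% in the other. It shows how the formula behaves and is not an expectation.

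**Cross-check.** A second set of scenarios used a pooled-variance test with fixed period counts, also at 135 per group. With recovery rising from 60% to 70%, late shares of 60/40, 70/30 and 80/20 give biases of 2, 4 and 6 points and false-positive rates of about 6%, 10% and 18%. With recovery rising from 60% to 80%, the same splits give 4, 8 and 12 points and about 10%, 30% and 58%.

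**With equal month mix in both groups** (d = 0), the bias is 0 for any trend and the rate is about 5%. The trend alone does no harm; the imbalance in enrolment time is also needed.

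**The case against.** The strongest reply is that no passage documents any drift. A reader might infer from the Discussion ("for the first time that TCM as an independent therapy included in the guideline to diagnoses and treat COVID-19") that the chance of receiving the granule rose during recruitment. That statement carries no date, and it concerns traditional Chinese medicine as a therapy in its own right, not this granule added to Western medicine. The Introduction also says the granule had been in use in Wuhan and elsewhere in Hubei since January 2020, before the study began, and three of the four centres are in Hubei. This does not prove stable uptake, but it weakens the inference.

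A reader might likewise infer changing Western care from the Introduction ("most antiviral drugs undergoing clinical testing in patients with COVID-19 are originally developed against influenza, HIV, Ebola, SARS, and MERS"). That describes uncertainty at one point in time, not a change between February and June. No passage reports a change in testing or hospital load, and section 2.10.1 applies one recovery definition to everyone.

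A reader might also call the controls non-concurrent. That is too strong: both groups are recruited prospectively in the same window, and Table 1 makes matching an enrolment step. What remains is only that the members of a pair may enter at different times within that window.

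Finally, the article is condensed, and date tolerances or adjustment covariates may sit in a fuller document. The silence of section 2.12 is thus weak evidence that no adjustment is planned. The point rests instead on section 2.8, which does name its factors and does say that they secure comparability. Admitting non-randomisation as a limitation does not support that statement.

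**Conclusion.** The point holds as a weakness in a stated design rule, not as a demonstrated bias. Three named factors cannot make non-randomised groups comparable on enrolment time, and nothing in the article limits or adjusts for it. Whether this matters depends on two quantities that the documents do not give: the difference in month mix between the groups and the trend in D14 outcome. Under the assumptions shown, the effect runs from close to negligible (2 points, about 6% false positives) to material (6 points, about 19%). The 12-point, 63% case should not be cited as a likely size. An inexpensive check and adjustment is warranted; the documents do not support a claim that the comparison is invalid.

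**What to change.** The study is in follow-up, so a calendar window added to the pairing rule can no longer govern enrolment. Keep the existing pairs and act in the analysis:

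1. Report the number of patients per group by month of D1, February to June 2020.
2. Stratify the primary D14 comparison by month of D1, or add month as a covariate in a logistic model. If the analysis is to respect the pairs, use the covariate, because a pair that spans two months cannot stay intact within month strata.
3. In section 2.8, say that the groups are paired on the three named factors, and drop the claim that this alone makes them comparable.

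The cost is one table, one model term or stratification factor, and one reworded sentence. Some precision is lost, and sparse months may have to be merged; the merging rule should be fixed before outcomes are compared. No new data should be needed, since Table 1 places consent at D1 and a date should exist, although the case report form is not shown. If the month mix proves balanced, the table itself supports comparability on enrolment time.
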